### Care as usual

All parents, both in the intervention and in the control group, receive the regular basic preventive care from their PCH organization including periodic health check-ups, the monitoring of growth and development, advice e.g. on safety, lifestyle and parenting, and possible referral to other services. Additionally, the intervention group receives the Individual Shantala Infant Massage intervention as part of selective preventive care provided by their PCH organization.

### Procedure

The study consists of three measurement moments: a pre-test (T0; at inclusion), a post-test (T1; post-intervention (intervention group) or approximately four weeks after T0 (control group), and follow-up (T2; when the child is 5 months old). Table 1 provides an overview of the various measurements at different timepoints.

**Table 1 Tab1:** Overview of study measurements and timepoints

Construct	Measure	Timepoint of assessment:			
		**T0** **(pre-test)**	**T1** **(post-test)**	**T2** **(follow-up)**	**Other, namely:**
***Evaluation of intervention effects*** ***Research questions 1, 2 and 3***					
**Primary outcomes**					
Parental stress					
• Perceived stress	Questionnaire:				
	• Perceived stress Scale (PSS-10, [41])	**x**	**x**	**x**	
	•Postpartum Specific Anxiety Scale Research Short-Form (PSAS-RSF, 42)	**x**	**x**	**x**	
• Physiological stress	Hair cortisol [43, 44]				A tuft of hair of the parent will be assessed at T2. By dividing the hair tuft in segments, cortisol levels can be assessed retrospectively to compare pre- and post-intervention levels
Parental sensitive responsiveness	Questionnaire:				
	• Non-responsiveness scale (MRQ, [45])	**x**	**x**	**x**	
	• Mother-to-infant bonding scale (MIBS, [46])	**x**	**x**	**x**	
	• Questionnaire: Cry perception [47]	**x**	**x**	**x**	
Growth and development of the infant	PCH assessments: • Length • Weight • Van Wiechen scheme, [48]				Length, weight and Van Wiechen scores are assessed during each standard PCH contact moment. All data points from birth up to six months will be obtained from PCH files
**Secondary outcomes**					
Parenting confidence	Questionnaire:				
	• Karitane Parenting Confidence scale (KPCS, [49]	**x**	**x**	**x**	
Parental concerns with regard to crying feeding, sleeping of the infant	Questionnaire:				
	• Likert scales	**x**	**x**	**x**	
**Other measurements**					
Parent (and family) characteristics	Questionnaire:				
	• Date of birth	**x**			
	• Gender	**x**			
	• Country of birth of responding parent and his/her parents	**x**			
	• Educational level	**x**			
	• Relationship status	**x**			
	• Living situation (living with/without partner)	**x**			
	• Health	**x**	**x**	**x**	
	• Sleep	**x**	**x**	**x**	
	• Anxiety and depressive symptoms of the responding parent (Hospital Anxiety and Depression Scale (HADS[50, 51])	**x**			
	• Employment and working hours			**x**	
Infant characteristics	Questionnaire:				
	• Parity	**x**			
	• Single or multiple birth	**x**			
	• Gestational age	**x**			
	• Gender	**x**			
	• Birth weight	**x**			
	• Health	**x**	**x**	**x**	
Other	Questionnaire:				
	• Infant carrying	**x**	**x**	**x**	
	• Experience with infant massage	**x**	**x**	**x**	
	• (Breast)feeding			**x**	
	• Use of childcare			**x**	
	• The occurrence of stressful life events during the study period			**x**	
	• Received support from- and satisfaction with PCH			**x**	
***Evaluation of the intervention process*** ***Research question 4***					
Evaluation of the intervention by participating parents	Evaluation questionnaire (participating parents)		**x**		
Process of the intervention	Logbooks of the intervention sessions (PCH nurses)				Semi-structured logbooks will be completed after each intervention session
Intervention experiences of professionals (PCH nurses) and participating parents	Individual interviews with a number of PCH nurses and participating parents				A number of PCH nurses and parents who finished the intervention will be interviewed

The study consists of three measurement moments: a pre-test (T0; at inclusion), a post-test (T1; post-intervention (intervention group) or approximately four weeks after T0 (control group), and follow-up (T2; when the child is 5 months old)

Parents complete questionnaires at T0, T1, and T2. All questionnaires are administered digitally via a secure website by default, but participants can receive a paper version upon request. At T2, a tuft of hair is cut from the parents’ head for the assessment of hair cortisol levels. The hair is cut during the 5-month contact moment at the PCH organization or at home by a member of the research team, depending on the PCH organization. Data on infant growth and development from birth up to six months that are collected by PCH as part of standard care, will be obtained from the PCH files.

In the intervention group, additional data is collected for the purpose of process evaluation. Between T0 and T1, the nurses carrying out the intervention keep semi-structured logbooks of the intervention sessions. At T1, parents complete an extra evaluation questionnaire. Finally, interviews are conducted with a number of parents and professionals.

## Measures

### Primary outcome measures

#### Parental stress

*Perceived stress.* Perceived parental stress is measured using two self-report questionnaires: the Perceived Stress Scale (PSS-10, [41]) and the Postpartum Specific Anxiety Scale Research Short-Form (PSAS-RSF, [42]. The PSS-10 is a widely used instrument that measures the degree to which participants appraise situations as stressful and current levels of experienced stress. It consists of 10 items of a general nature. Example items are “How often have you been upset because of something that happened unexpectedly?” and “How often have you found that you could not cope with all the things that you had to do?”. For each item, participants are asked to indicate on a 5-point scale how often they felt or thought that certain way in the last month. Answer options range from 0 “never” to 4 “very often”. Total scores are calculated by reversing positively stated items and subsequently summing all items. A higher total score indicates a higher level of perceived stress. In addition to general perceived stress, maternal- and infant-focused concerns specific to the postpartum period are measured with the PSAS-RSF [42]. The PSAS-RSF is a shortened version of the PSAS, a validated 51-item instrument to measure postpartum anxiety [52]. The PSAS-RSF consists of 16 items and comprises four domains: (1) psychosocial adjustment to motherhood; (2) practical infant care anxieties; (3) maternal competence and attachment anxieties; and (4) infant safety and welfare anxieties. The measure demonstrated good construct validity and overall reliability [42]. Example items are “I have worried I will not know what to do when my baby cries” and “I have worried about my baby’s milk intake”. Participants are asked to rate each item with the answer that comes closest to how they have felt in the past 7 days, on a 4-point scale ranging from 1 “not at all” to 4 “almost always”. A total score and subscale scores can be calculated by summation of the individual item scores. Higher scores reflect higher levels of postpartum anxiety.

*Physiological stress.* Parents’ physiological stress levels are measured in hair cortisol; a reliable and valid measure for physiological stress [43, 44, 53]. The measurement of hair cortisol is a non-invasive and safe method, that provides insight in the accumulation of the cortisol stress hormone over the past months. The hair sampling is done during the 5 months contact moment (T2) at the PCH organization or at the participants’ home. About 100 hairs are cut on the back of the head, close to the scalp. The place is not visible afterwards. The tufts of hair are divided into segments of 2 cm each, enabling the comparison of stress levels before and after the intervention (i.e., pre- and posttest) between parents in the intervention and the control group. Cortisol analyses are outsourced to Dresden LabService GmbH [54].

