**Methods:**

The study is a quasi-experimental non-randomized trial. The aim is to include 150 infant-parent dyads in both the intervention and the control group. This takes into account possible attrition and missing data as 105 dyads with complete data per group are sufficient for analysis. All participants complete questionnaires at T0 (pre-test, child age between six-sixteen weeks), T1 (post-intervention, or ± four weeks after T0), and T2 (follow-up at five months). At T2, a hair tuft is cut from the parents’ head to measure hair cortisol levels. Data on infant growth and development is obtained from PCH files. In the intervention group, additional data is collected to evaluate the intervention process: parents complete an evaluation questionnaire at T1, nurses keep semi-structured logbooks of intervention sessions and interviews are conducted with parents and professionals.

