**Fig. 2 Fig2:**
[figure not shown]
Flow chart of the non-randomized controlled trial

The intervention group is recruited via two PCH organizations that both offer Shantala Infant Massage as a preventive intervention: Child and Family Centre Rijnmond (In Dutch: Centrum voor Jeugd en Gezin Rijnmond) in the city of Rotterdam and PCH Kennemerland (In Dutch: Jeugdgezondheidszorg Kennemerland) in Haarlem and surrounding (rural) areas. Parent–child dyads are eligible for participation in the study when they are about to engage in the Individual Shantala Infant Massage intervention, the infant is younger than 16 weeks and the parent is able to understand the study information and to complete the questionnaires in Dutch or English, with assistance if necessary. The parent taking part in the infant massage, is invited to participate in the study.

Participants of the control group are recruited via the PCH organization in Amsterdam, which is part of the GGD Amsterdam. Recruitment is focused on 7 PCH locations within three specific areas of the Amsterdam region with relatively high rates of vulnerability in multiple domains. Inclusion criteria for parent–child dyads regarding the age of the infant and language understanding are similar as for the intervention group. The parent who spends most time with the infant is invited to participate in the study.

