For both the intervention and control group, suitable participants are notified of the study by PCH professionals. Contact information of interested parents is forwarded to the researchers with permission of the parents. Parents receive additional information on the research in a simple and accessible format. Participant information is provided in a written format, as well as in videos on a project website. To avoid desirable answers in the intervention group and to make participation more appealing for the control group, there is no emphasis on the effects of infant massage in the participant information. Instead, the focus of the study is described more generally, namely, the study is described as being about the wellbeing of infants and parents in the first 6 months and the support provided by PCH organizations during this period, including infant massage. Furthermore, parents are informed about the collection, storage, use and reuse of the data (note that in the Code of Conduct for Medical Research, ‘reuse’ is also referred to as ‘further use’), privacy regulations and rights under GDPR and contact information of the research team in case of complaints or questions.

The parents are given time (a couple of days) to consider participation. Parents’ (digital) consent form precedes the pre-test questionnaire. In case the informed consent form and the questionnaire are not yet completed after some time, the researchers contact the parents via e-mail and/or phone to check if everything was clear and as a reminder. For the intervention group, it is important that the first questionnaire is completed before the start of the intervention. All parents who provide informed consent and complete the first questionnaire are enrolled in the study. After their study participation is completed, participants receive a gift voucher of 15 euros as a thank-you.

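### Fixed 2-cm hair segments cut at five months cannot separate pre- from post-intervention cortisol for all dyads, because T0 ranges over ten weeks of infant age

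*Protocol article*

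**What the plan says.** Under Primary outcome measures, Parental stress (physiological stress), the protocol article describes one tuft per parent, cut at the five-month contact (T2), and states: "The tufts of hair are divided into segments of 2 cm each, enabling the comparison of stress levels before and after the intervention". Table 1 repeats the claim: "By dividing the hair tuft in segments, cortisol levels can be assessed retrospectively to compare pre- and post-intervention levels".

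The abstract places T0 at "child age between six-sixteen weeks", and the Recruitment section admits dyads when "the infant is younger than 16 weeks". For the intervention arm, "it is important that the first questionnaire is completed before the start of the intervention". The intervention is three weekly visits. T1 follows the intervention, or comes about four weeks after T0 in controls. The Statistical analysis section compares groups at T1 and T2 with correction for the T0 measures.

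The article gives no hair growth rate. It does not say how many segments are assayed or which one counts as pre, and it does not tie segments to any parent's own dates.

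**The concern.** A segment's time window is counted back from the hair cut, and the cut is at one infant age for all. The intervention is timed from T0, which varies by ten weeks. A boundary fixed on the first clock cannot track an event on the second. For early entrants the older segment takes in time after the intervention began; for late entrants the newer segment takes in time before it.

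This matters more here than in a randomised trial. Intervention parents are offered the programme because professionals see risk signals, while controls are recruited by area. The Discussion relies on the pre-post design to limit the effect of non-randomisation. No hair is taken at T0, so a retrospective segment is the only possible cortisol baseline. If that baseline is partly post-treatment, a null or small cortisol result is hard to interpret.

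**Working it through.** The plan states no figure for the window a segment covers, so there is none to reproduce.

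**Inputs from the protocol article:** one cut at 5 months (5 x 4.348 = 21.74 weeks); 2-cm segments; T0 from 6 to 16 weeks; intervention after T0.

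**Assumptions, not in the document:** growth g of 0.8, 1.0 or 1.2 cm/month; T0 uniform over 6-16 weeks; gap of 0, 1 or 2 weeks from T0 to first visit; 0-2 cm segment (segment 1) as post and 2-4 cm segment (segment 2) as pre.

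**Step 1: a result that needs no growth rate.** Let B be the infant age at the boundary between segments 1 and 2. Segment 2 is purely pre only if B is at or before the intervention start. Segment 1 is purely post only if B is at or after it. Both hold only when the start equals B, which is one entry age in the whole range. If the intervention weeks count as neither pre nor post, B would have to be both at or before T0 and at or after T1, which no entry age satisfies.

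**Step 2: windows.** Segment length in weeks is L = (2/g) x 4.348, and B = 21.74 - L. At 1 cm/month, L = 8.70 and B = 13.04. Segment 1 covers 13.0-21.7 weeks and segment 2 covers 4.3-13.0 weeks.

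- Start at 6 weeks: (13.04 - 6)/8.70 = 81% of segment 2 lies after the start.
- Start at 10 weeks: 35%.
- Start at 13 weeks: about 0%, so both segments are clean.
- Start at 16 weeks: (16 - 13.04)/8.70 = 34% of segment 1 lies before the start.

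**Step 3: how many intervention dyads have a contaminated segment 2.** The share is (B - gap - 6)/10.

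| Growth (cm/month) | B (weeks) | Gap 0 | Gap 1 wk | Gap 2 wk |
|---|---|---|---|---|
| 0.8 | 10.9 | 49% | 39% | 29% |
| 1.0 | 13.0 | 70% | 60% | 50% |
| 1.2 | 14.5 | 85% | 75% | 65% |

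The entry distribution matters too. At 1.0 cm/month with no gap, entry skewed early (Beta(1,2)) gives 91% and entry skewed late (Beta(2,1)) gives 50%.

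**Step 4: how much of a sustained effect survives.** Take a constant effect from the start, no gap, at 1 cm/month. The mean post-start share is:

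- segment 1: 1 - (16 - 13.04)^2/(2 x 8.70 x 10) = 0.95
- segment 2: (13.04 - 6)^2/(2 x 8.70 x 10) = 0.285

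Retained effect:

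- Change score (segment 1 minus segment 2): 0.95 - 0.285 = about 66%. At 0.8 cm/month it is 77% and at 1.2 cm/month 50%.
- Segment 1 adjusted for segment 2 with baseline slope b: 0.95 - 0.285b. Assumed slopes of 0.3, 0.5 and 0.7 give 86%, 81% and 75%.
- Segment 1 alone: 95%, with no baseline.

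**The case against.** **The article is condensed, and assigning segments to windows belongs in a full analysis plan.** That is fair for the number of segments and the growth rate, and their absence is not the point. The article goes further and asserts, twice, that the segments enable the pre/post comparison. Its own schedule does not support that.

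**Segment 2 is never named as the pre segment.** True. A third segment (4-6 cm) would lie before every T0 at 1 cm/month. But it covers about 4.3 weeks before birth to 4.3 weeks after, needs 6 cm of hair, and leaves the late entrants' problem in segment 1 untouched.

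Four stronger readings are tempting but not supported:

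- *The baseline is contaminated in most dyads.* This depends on growth rate, gap and entry distribution, none of which is given. The range under uniform entry crosses one half.
- *Power falls from 0.90 to about 0.58.* That follows from putting 66% of d = 0.50 into the two-group calculation with 84 per arm. It describes a change score and ignores that score's standard deviation. The plan corrects for baseline, which loses less.
- *The bias is always towards no effect.* This needs a sustained effect. An effect that fades after the visits could even reverse a change score, and confounding can act either way.
- *Everyone enrolled before about 13 weeks is adjusted for a post-treatment value.* Controls receive no intervention, so only intervention dyads are affected.

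The questionnaire stress outcomes also have true T0 values, so the defect is confined to cortisol.

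**Conclusion.** The point holds in this limited form: one boundary fixed relative to T2 cannot separate pre from post for all dyads when T0 spans 6 to 16 weeks, so the enabling statement in the text and in Table 1 should not stand. That conclusion rests on the protocol's schedule alone.

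The size is conditional on the assumptions listed in the working. Centrally, about 70% of intervention dyads have a contaminated 2-4 cm segment, and a baseline-adjusted comparison keeps roughly three quarters to seven eighths of a sustained effect. The comparison is diluted, not absent. Severity: should-fix.

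**What to change.** 1. Remove the statement that the fixed segments represent pre and post, in the text and in Table 1.
2. State the assumed growth rate. Compute each segment's window from the hair-cut date and set it against that parent's own T0, T1 and, where it exists, first-visit date.
3. Use a segment as baseline covariate only if its window ends by T0, with the same date rule in both arms. T0 is the date both arms share; a first-visit rule would need a matching reference date for controls.
4. Where no segment qualifies, model cortisol (transformed if skewed) across each parent's segments on group, segment position, the fraction of the segment after T0, and group x post-T0 fraction. The interaction carries the treatment effect. Leave out a separate weeks-postpartum term: with all hair cut at about five months it is nearly collinear with segment position.
5. Repeat at 0.8 and 1.2 cm/month.

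Samples and assays are unchanged, but this redefines how a primary outcome is estimated, so it should be settled before the cortisol data are analysed. The cost is a wider interval and fewer parents with a usable cortisol baseline. The interaction also draws on differences in entry age that were not randomised, which should be acknowledged when it is reported.

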#### Parental sensitive responsiveness

We operationalize the degree of parental sensitive responsiveness with three measures: the Non-Responsiveness Scale from the Maternal Responsiveness Questionnaire (MRQ, [45]), the Mother-to-Infant Bonding Scale (MIBS; [46]), and the Cry Perception Scale [47].

In the MRQ [45] seven contexts are presented, for example “When your baby is crying because he or she is sick or ill (e.g., has a cold, is teething, is feeling poorly after shots)” and “When your baby is crying even though he or she is well fed, well-rested, and has a fresh diaper”. For each context, different responses are described and participants are asked to rate how likely they are to respond in that specific way on a 5-point scale ranging from 1 “never” to 5 “always”. The full MRQ consists of three subscales (responsiveness, non-responsiveness, delayed responsiveness), with corresponding responses to the seven contexts. In this study, we only include the non-responsive scale with the corresponding responses: "You let your child cry for 10 min before you respond" and "You let your child cry until your child stops crying, no matter how long this takes". In combination with the seven contexts, the non-responsiveness scale consists of 13 items. Total scores of this subscale can vary between 13 and 65, with higher scores indicating less sensitive responsive behavior [45].

The MIBS [46] aims to measure feelings of parents towards their newborn babies. Parents are asked to indicate on four-point Likert scales ranging from "Very much" to "Not at all" to what extent each of the following eight feelings apply to them: “Loving, Irritated, Neutral, Happy, Dislike, Protective, Disappointed and Angry.” Total scores can vary between 0 and 24, with higher scores indicating more problematic feelings of the parent toward the infant and worse mother-to-infant bonding [46].

The Cry Perception Scale [47] measures the parents' perception of their infant's crying, using twelve 7-point bipolar rating scales. First, parents are asked in eight items how their child's cry sounds (e.g. not urgent to urgent, healthy to sick, uplifting to uncomfortable). Higher scores indicate a more negative perception of crying. Subsequently, the parent is asked to rate three items about how he / she feels when the infant is crying (e.g. not irritated to irritated, not sad at all to extremely sad). Higher scores indicate a more negative feeling. Finally, parents are asked whether their child's crying gives them the feeling of wanting to take care of the child (1 “not at all” to 7 “absolutely).

#### Child growth and development

Data on infant growth (weight and length) and development (the Van Wiechen Scheme [48, 55] from birth up to six months are obtained from files of the PCH organizations, as these data are collected as part of standard care during regular PCH contact moments.

A standard deviation score (SDS) will be calculated for weight and length for every measurement moment. This number indicates the difference with respect to the gender and age-specific average, expressed in standard deviations, enabling comparisons over time and between groups.

The Van Wiechen Scheme is the Dutch equivalent of the Bayley scales and is used to measure development in children in a systematic way [56]. It consists of developmental indicators in different domains including gross and fine motor skills, adaptation, language development, social behavior and personality. At every PCH appointment, an age-appropriate set of indicators is administered by the PCH professional [55]. These standard sets are selected in a way that about 90 percent of the children will pass. The scores on the separate Van Wiechen indicators will be used to determine a quantitative D-score (developmental score) as a continuous measure for the child’s global development. By means of the D-score it can be made clear whether a child develops according to the norms. The D-score can be used to measure differences between groups and to evaluate interventions [56].

